## Discussion

8

By reason of the high prevalence of PSCIND and high social acceptability of acupuncture in China, we have the advantage on conducting large-sample research. This protocol design also has additional strengths. First, as far as we know, we are the first randomized controlled trial to study if acupuncture has efficacy on preventing PSCIND progressing to PSD; second, avoiding false increase of patients’ cognitive-function test results caused by multiple use of same scale. We measure the cognitive function with different version of MoCA, including 7.1, 7.2, 7.3, and basic of MoCA; third, multicenter. Our trial will be conducted in 5 inpatient and outpatient stroke rehabilitation units of different cities, which can ensure the sample representativeness. Fourth, a 12-week intervention and 24-week follow-up assessment can provide reliable long-term effect evidence for acupuncture on improving cognitive function, mental state, and quality of life for PSCIND patients.

On the contrary, this protocol design also has limitations, which are as follows. There could be a very few overlaps exists between early stage of AD and PSCIND in our participants. Fifty-six percent of all demented cases are the patients who suffer from AD with stroke.^[41]^ A Study also shows that the atherosclerosis, which is one of the common causes of stroke, may also have effects on the pathogenesis of AD.^[42]^ We can see that the inner correlation may exist between stroke and AD. Therefore, the participants in our trail may also suffer both AD and PSCI. And this will affect the evaluation of the outcome in this study. Potential spontaneous recovery at the early stage of stroke may have the confounding effects on this trial, but the waiting-list group can reduce the effects of it. Due to the limitations of equipment and capital, only part of the participants will get the fMRI scan. This may affect the generalizability of the results.

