### Inclusion criteria

2.3

Patients are eligible for study inclusion if they

(1)Meet the diagnostic criteria of ischemic stroke^[18]^(2)Meet the diagnostic criteria of PSCIND^[7,19–21]^

(1)Have the ability to take care of themselves in daily life. Barthel index ≥60.(2)Montreal cognitive assessment scale (MoCA) < 26(3)Mini-mental State Examination (MMSE): MMSE Score >17 (illiteracy), or MMSE score > 20 (primary school culture), or MMSE score >24 (middle school and above);(4)Ischemic stroke within 6 months;(5)Men or women aged 18 to 75 years;(6)The patients sign informed consent and cooperate with the treatment.

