### Sample size and statistical methods

7.5

The sample size calculation is based on the improvement of Montreal cognitive assessment scale (MoCA) scores, which has a higher sensitivity than MMSE for MCI.^[7]^ According to the similar published articles,^[40]^ the mean difference in MoCA scores between AG and control group (CG) is 1.5, with a standard deviation of 1.13 in AG and 1.20 in CG. According to our previous study, acupuncture treatment can probably improve the MoCA by 0.6 on average compared with control group. Considering a 1-sided significance level of 0.025 and power of 95%, 95 participants are required for each group, as calculated by PASS 11 software. To minimize attrition bias, we assumed the dropout rate of 20%, making it necessary to include at least 357 participants with a 1:1:1 group allocation rate. We plan to enroll 360 participants in total.

Continuous variables are presented as mean (SD) if they obey normal distribution, and paired-sample *t* test will be used in intragroup comparison; if they are not normal distribution, median (quartile interval) [M(IQR)] will present them, and Wilcoxon rank sum test will be used in intra-group comparison; Variance analysis will be used for comparison between groups which is consistent with the normal distribution and homogeneity of variance; if not, then Mann–Whitney *U* test will be used. Group comparisons will then be undertaken using χ^2^ tests for categorical characteristics. Two-sided *P* < .05 represents statistical significance for all the analyses.

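### Before-after tests within each arm carry the same significance rule as the between-arm tests, so natural recovery alone can count as a significant gain

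*Protocol article*

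**What the plan says.** Four places in the protocol article bear on this.

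- **Inclusion criteria (2.3).** The timing criterion is "Ischemic stroke within 6 months". It sets an upper limit and no lower one. The Discussion adds: "Our trial will be conducted in 5 inpatient and outpatient stroke rehabilitation units of different cities".
- **Statistical methods (7.5), within arms.** For normally distributed continuous variables, a "paired-sample *t* test will be used in intragroup comparison"; otherwise a rank test.
- **Statistical methods (7.5), between arms.** "Variance analysis will be used for comparison between groups which is consistent with the normal distribution and homogeneity of variance", with Mann-Whitney as the fallback and chi-square for categorical data. No covariate is named. The paragraph closes with one rule for both kinds of test: "Two-sided *P* < .05 represents statistical significance for all the analyses".
- **Discussion (8).** Among the limitations: "Potential spontaneous recovery at the early stage of stroke may have the confounding effects on this trial, but the waiting-list group can reduce the effects".

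The trial is randomised 1:1:1 to acupuncture, sham or waiting list (2.2, 2.7). The waiting-list arm receives standard treatment only for 36 weeks (3.3).

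**The concern.** The sponsor names spontaneous recovery as a threat and relies on the waiting-list arm to deal with it. A concurrent untreated arm removes recovery from a difference between arms. It does nothing for a test that compares one arm with its own baseline, because in that test recovery and any effect of acupuncture are the same quantity.

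Section 7.5 plans both kinds of test, gives them the same threshold, and neither ranks them nor calls the within-arm ones descriptive. The objective (2.1) is efficacy on cognition, daily living, mental state and quality of life. As the text stands, a significant before-after gain in the acupuncture arm could be reported as a positive finding on any of these, even if the waiting-list arm improved just as much.

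**Working it through.** **The plan's own figure.** Section 7.5 gives a 0.6-point MoCA difference, SDs of 1.13 and 1.20, one-sided alpha 0.025, 95% power and 95 per group.

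- Common SD = √[(1.13² + 1.20²)/2] = 1.166.
- n = 2 × (1.960 + 1.645)² × 1.166² / 0.6² = 98.1, so 99 per group against the stated 95.
- Power at 95 per group is 94.2% (noncentral t), close to the stated 95%.
- Dropout: 95/0.80 = 118.75, so 119; 3 × 119 = 357, as stated.

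The gap between 95 and 99 is small and nothing below depends on it. What matters is that the trial is sized on a between-arm difference.

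**Smallest within-arm gain that is significant.** Gain = t(0.975; 94 df) × SD/√95, with t = 1.986 and √95 = 9.747. The article does not give an SD of change, so its planning SDs are used first and 2 and 3 as a wider assumed range.

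| SD of change | Smallest significant mean gain (MoCA points) |
|---|---|
| 1.13 | 0.23 |
| 1.20 | 0.24 |
| 2 | 0.41 |
| 3 | 0.61 |

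At the planning SDs this is less than half the 0.6 points that the trial is designed to detect between arms.

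**How often an arm with no treatment effect shows a significant gain.** The size of natural recovery is not in the article; 0.5 and 1.0 points are assumptions. Paired t test, n = 95, two-sided 0.05, noncentrality = gain/(SD/√95). For a gain of 0.5 this is 4.17, 2.44 and 1.62 at SD 1.17, 2 and 3.

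| Natural gain | SD 1.17 | SD 2 | SD 3 |
|---|---|---|---|
| 0.5 | 98% | 67% | 36% |
| 1.0 | 100% | 99.8% | 90% |

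These are not type I errors of the paired test, since the change over time is real. They show how often the plan would label an ineffective treatment arm as significantly improved.

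**The between-arm comparison.** Three arms of 96 (120 less 20%) were simulated 4,000 times per setting. Entry times were uniform over 0 to 6 months, recovery fell linearly to zero at 6 months, and the residual SD was 1.166. Mean recovery was set to 0, 0.5, 1.0 or 2.0 points.

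- With no acupuncture effect, the mean difference between acupuncture and waiting list was between -0.004 and 0.002, and the three-arm variance analysis rejected in 4.8% to 5.7% of runs. There is no systematic bias.
- With mean recovery 1.0, recovery runs from 2 to 0 points and its SD is 2/√12 = 0.577. Chance imbalance in entry time then shifts the difference by 1.96 × 0.577 × √(2/96) = ±0.16 points. The ordinary standard error already includes this.
- Power for 0.6 points, unadjusted versus adjusted for time since stroke: 92.9% versus 94.1% at mean recovery 0.5; 88.4% versus 93.7% at 1.0; 70.0% versus 94.5% at 2.0.

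**The case against.** The strongest reply is that nothing in the article says efficacy will be judged by within-arm change. The trial is randomised with sham and untreated arms, section 7.5 plans between-arm tests, and the sample size rests on a between-arm effect. The Discussion says only that the waiting list can reduce the effect of recovery, which is true of the randomised contrasts. All of this stands, and it means that a misleading claim is possible, not certain. It does not remove the point: the stated rule gives the before-after tests full significance status.

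Several stronger readings are tempting, but the document does not support them.

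- **Recovery confounds the comparison between arms.** A reader might infer this from the wide entry window. Randomisation makes recovery equal across arms in expectation, and the simulation shows no bias.
- **Patients enter in the acute phase.** The article does not say so. Only the lack of a lower limit is stated, and the Barthel criterion and recruitment from rehabilitation units narrow who can enter.
- **Selection on low scores inflates every scale.** Entry at MoCA below 26 could push MoCA upward on retest. MMSE entry is above education-specific floors, which pushes the other way, and there is no entry criterion on FAQ, NPI or quality of life.
- **Time since stroke is ignored in allocation.** The dynamic allocation factors are not listed, but an article commonly leaves them to the full protocol.
- **The power loss is established.** It depends on assumed recovery. If the planning SDs already contain that spread, the sample size already allows for it.

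**Conclusion.** The point holds as a matter of how significance is defined in section 7.5. Within-arm tests count as statistical significance on the same footing as between-arm tests, in a population where the protocol itself expects natural improvement, and the safeguard it cites cannot protect those tests.

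The size depends on two quantities that the article does not give: the natural gain and the SD of change. Across the assumed range, an arm with no treatment effect would show a significant MoCA gain in 36% to practically 100% of cases. The validity of the between-arm comparison is not in question; there, uneven recovery can cost only precision, by an unknown and possibly small amount.

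**What to change.** 1. **Section 7.5.** State that efficacy is judged only by between-arm differences, acupuncture versus sham and acupuncture versus waiting list. Report within-arm change as a mean with confidence interval, without a P value or claim of significance, and confine the P < .05 rule to the between-arm analyses.
2. **Discussion (8).** Limit the sentence on spontaneous recovery: the waiting-list arm accounts for it in between-arm contrasts, not in before-after change within an arm.
3. **Optional, for precision.** Include time from stroke onset to randomisation as a covariate in the between-arm analysis. This corrects no bias, and the gain may be small if the planning SDs already include the spread in recovery.

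The cost is a few sentences. Eligibility already requires the time of the stroke, so no new data are needed, and sample size, treatment and visits do not change.

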## Ethics approval and consent to participate

9

The ethic committee of First Teaching Hospital of University of Traditional Chinese Medicine approved the study. We have also registered at ClinicalTrials.gov (http://www.chictr.org.cn/showprojen.aspx?proj=54764): ChiCTR2000033801. All patients gave their written informed consent before participating in the clinical trial. The details of our study, including trial objectives, characteristics, probable benefits and risks, other available treatment alternatives, and the subjects’ rights as well as obligations as stated in the Declaration of Helsinki, will be made clear to the patients by a study personnel who has their grouping code, and their agreement will be required. After obtaining the written informed consent, the subjects will be enrolled in the study. During the process of the trial, if new points regarding the study ethics emerge, written revisions regarding the informed consent will be handled by the Ethics Committee and, after their approval, the individuals’ consent will be requested again. In case of the patients’ withdrawal, their available data will be kept for the final analyses.

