### Recruitment strategies and randomization

2.7

The study population is patients who had Post-stroke Cognitive Impairment with no dementia. We will recruit 360 eligible patients from five hospitals in China: The First Teaching Hospital of Tianjin University of traditional Chinese medicine (TCM), The Changchun hospital of TCM, Changzhi City of Traditional Chinese Medicine affiliated hospital, Changsha central hospital, The Second affiliated hospital of Baotou. Recruitment posters will be used in every participating hospital. We also use the various social media platforms to distribute the trial information. The eligible patients must satisfy the criteria defined below. Patients who express a general interest in taking part in the study will be informed of all necessary information in oral and written form. After fulfilling the criteria and signing the consent, the study personnel will assign the patient to the acupuncturist who is in charge of the patient.

A full-time staff of The First Teaching Hospital of Tianjin University of TCM will randomize all the eligible participants into the AG, NAG, or the WLG in a 1:1:1 ratio by a dynamic random allocation technique.

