### Blinding

2.8

Assessors who are masked to treatment allocation and trained will be in charge of baseline evaluation and measurement. Patients who receive acupuncture treatment will not be aware of their group assignment. However, the waiting-list group cannot be blinded. Because different acupuncture treatments are used in AG and NAG, it is impossible to blind the acupuncturists. During the trial period and follow-up phases, the third party and assessors will all be blinded.

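### Section 9 gives the patient's grouping code to the person seeking consent, before enrolment; as written this breaks allocation concealment and conflicts with sections 2.3 and 2.7

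*Protocol article*

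**What the plan says.** Section 9 of the protocol article describes the consent conversation. The content of the trial "will be made clear to the patients by a study personnel who has their grouping code", and the patient's agreement is sought at the same point. The next step is "After obtaining the written informed consent, the subjects will be enrolled in the study".

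Three other sections bear on the order of events:

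- Section 2.3 (Inclusion criteria) lists as a condition of eligibility: "The patients sign informed consent and cooperate with the treatment".
- Section 2.7 (Recruitment strategies and randomization) says: "After fulfilling the criteria and signing the consent, the study personnel will assign the patient to the acupuncturist who is in charge of the patient". It then says that a full-time staff member of the lead hospital "will randomize all the eligible participants into the AG, NAG, or the WLG in a 1:1:1 ratio by a dynamic random allocation technique".
- Section 2.8 (Blinding) names the assessors and the third party as blinded and says of the treated patients: "Patients who receive acupuncture treatment will not be aware of their group assignment". It accepts that the acupuncturists and the waiting-list group cannot be blinded. It does not mention the staff who take consent.

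**The concern.** Randomisation protects the comparison only if nobody who influences a patient's entry knows the arm that the patient would get. Section 9 places a code for the group with the person who presents the trial and asks for agreement, at a point when the patient has not yet been enrolled. If that person can read the arm from the code, the choice of whom to approach, how to describe the trial, and whether to press or let go can all depend on the arm.

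The three arms differ in their appeal to a patient and to a recruiter: real acupuncture, sham acupuncture, and a waiting list with standard treatment only for 36 weeks (section 3.3). The waiting list is the arm most exposed, because it is open and offers no trial treatment during that time. If patients who would be sent to it decline or are steered away more often, those who remain may differ in motivation, support at home or expected recovery. Patients here are within 6 months of an ischaemic stroke, and the article itself names spontaneous recovery as a possible confounder (section 8). It relies on the waiting-list group to reduce that confounding, so selective entry into that group would weaken the safeguard.

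**Working it through.** There is no figure to recompute. The check is whether the sections describe one order of events.

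**Order in section 9.**
1. Staff holding the patient's grouping code explain the trial.
2. The patient gives written consent.
3. The patient is enrolled.

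Here the code exists at step 1, before both consent and enrolment.

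**Order implied by sections 2.3 and 2.7.**
1. The patient is found to meet the criteria. One of these is signed consent, so eligibility is not complete without it.
2. The lead-hospital staff member randomises the eligible participants. Because eligibility includes consent, this can only follow consent.
3. The allocation is dynamic. Such a method ordinarily produces an assignment when a patient is entered, rather than reading it from a list prepared for named patients.

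Here no individual assignment should exist when the trial is explained.

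**Comparison.** Section 9 requires a group code at the consent conversation; sections 2.3 and 2.7 imply that there is none. If the code identifies the arm, both accounts cannot be followed. Section 2.7 does not settle the matter expressly. It puts assignment to an acupuncturist after consent, but it does not say where the randomisation step falls relative to consent. The order has to be inferred from the word eligible together with section 2.3.

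**Does blinding close the gap?** No. Section 2.8 concerns treated patients, assessors and the third party. The consent-taker is not among them, and blinding after allocation does not replace concealment before it.

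**Could the code be harmless?** The term is not defined. Section 5 (Data management and quality control) uses pre-set codes for the files holding personal information, which are identifiers. Section 9 uses a different term, one that refers to the group. The ordinary meaning is a code for the allocated arm, although a masked code is not excluded.

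**The case against.** The strongest reply is that one clause in an ethics paragraph is weak evidence of the actual procedure. The sections that describe recruitment point to consent first and randomisation second. The same ethics paragraph is loose elsewhere: it says patients have given consent and then that agreement will be required, and it names one registry while giving another's number and link. The code is undefined and might be masked. A condensed article may also leave the concealment mechanism to the full protocol.

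Much of this stands. It means that the document does not establish that recruiters will in fact know the arm, and the absence of a described concealment mechanism is not counted against the article here. It does not remove the point, because the article makes a positive statement that, if followed, defeats concealment, and that statement contradicts its own recruitment section.

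Three stronger readings should be resisted:

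- A reader might infer that patient blinding between real and sham acupuncture is also compromised. Nothing says that the code is disclosed to patients, section 2.8 says treated patients will not know their group, and the acupuncturists who treat them are already openly unblinded. No additional route to unblinding is shown.
- A reader might set an assumed shift in prognosis against the 0.6-point MoCA effect in section 7.5. The document gives no basis for any such shift, so the ratio would only restate the assumption.
- A reader might say that the analysis could repair none of the resulting imbalance. Baseline MoCA, MMSE and CDR are collected (Table 3), so imbalance in those could be adjusted for. Imbalance in unmeasured prognosis could not.

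**Conclusion.** The point holds as a stated rule that breaks concealment if followed, and as a contradiction between section 9 and sections 2.3 and 2.7. It rests on two assumptions: that the grouping code identifies the allocated arm or can be read as doing so, and that sites may act on section 9 as written. If either is false, the damage is confined to the text.

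Selection bias is a risk here, not a demonstrated result. Its size cannot be computed from the document, and the waiting-list comparison is the most exposed. It is tempting to conclude that concealment is certainly absent from this trial. The document does not support that, because sections 2.3 and 2.7 imply the opposite order.

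It should still be corrected. Selective enrolment cannot be undone once patients are in, and the correction costs very little.

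**What to change.** In section 9, delete the clause that gives the consenting staff the grouping code. State instead that consent and baseline assessment are completed by staff without access to any allocation.

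In sections 9 and 2.7, state the same order: eligibility and consent, baseline assessment, irrevocable registration of the patient, then generation and release of the assignment by the lead-hospital randomiser. Name who receives it: designated unblinded site staff, namely the acupuncturist for the acupuncture and sham groups and a coordinator for the waiting list, and never the assessors. A rule that releases it to the acupuncturist alone would not work for the waiting list, which has no trial acupuncture in the first 36 weeks (section 3.3).

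If the grouping code was meant as a masked identifier, say so and define it.

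The cost is a few sentences in two sections and, if sites have been working as section 9 describes, a change in the order of steps. The randomising role at the lead hospital already exists. Each site would need to name someone to receive waiting-list assignments.

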## Dissemination

10

Study results will be first informed to each participant and later disseminated to researchers, and the general public through courses, presentations and the internet, regardless of the magnitude or direction of effect. The results will also be documented in a published peer-reviewed academic journal.

### Consent for publication

10.1

Not applicable.

### Availability of data and materials

10.2

The submitted manuscript is a study protocol that includes no primary data now. More data and materials unmentioned can be obtained from the corresponding author by the contact methods provided in the manuscript.

